#### *Secondary outcomes 6-9:*

Secondary outcomes 6, 7, 8, and 9 are descriptive in nature. These will be described using frequencies, stratified by country, site, and patient characteristics as numbers allow.

#### *Secondary outcome 10:*

We will estimate the average cost to patients per clinic visit using questionnaire responses, including transport, substitute labor, and other costs. This cost will then be multiplied by the average number of clinic visits observed in each study arm to generate a total average cost to patients of ART initiation under each model (SLATE and standard). Costs will be reported as means (standard deviations) and medians (IQRs) in local currencies and dollars.

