## **12. Outcomes and Data Analysis**

### *12a. Outcomes*

The primary outcomes for the study are:

1. The proportion of patients initiated on ART within 28 days of study enrollment. While national guidelines recommend ART initiation within two weeks of a patient's first clinic visit or HIV diagnosis, recent studies suggest that 28 days is a more realistic deadline for routine care.

2. The proportion of patients who initiate ART and are alive, in care, and retained on ART eight months after study enrollment. Eight months was selected to allow up to 1 month (28 days) to initiate ART, six months of follow up after treatment initiation, and up to 1 month to return for the six-month routine clinic visit.

These outcomes were proposed in a paper published by the investigators based on the MATI technical consultation described in protocol section 3c.

Secondary outcomes will include:

3. The proportion of patients initiated on ART within 14 days of having an HIV test or enrolling in HIV care.
4. The proportion of patients who initiate ART and are virally suppressed eight months of having an HIV test or enrolling in HIV care between HIV-infected patients offered immediate ART initiation under the SLATE algorithm and patients offered standard ART initiation.
5. The proportions of patients who initiate ART and are alive, in care, and retained on ART 14 and 16 months after having an HIV test or enrolling in HIV care. Fourteen months extends the primary outcome endpoint, which is at 8 months, by an additional six months. Sixteen months allows loss to follow up at 12 months to be defined as three months late for the 12-month visit, which is a common endpoint in the literature (16 = 1 month to initiate ART + 12 months' follow up + 3 months to attend 12-month visit).
6. The proportions of HIV-positive patients presenting at study clinics and not yet on ART who are eligible and ineligible for immediate initiation using SLATE algorithm criteria.
7. Reasons for ineligibility for immediate initiation, among those found ineligible in the intervention arm.
8. Average time to ART initiation (days) for each arm.
9. Patient preferences on the speed and timing of ART initiation.
10. Costs to patients of ART initiation under standard and intervention procedures.
11. Costs to providers of ART initiation under standard and intervention procedures.

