#### *Secondary outcome 11:*

At 8 months after study enrollment, all resource usage will be extracted from subjects' medical records and case report forms. Unit costs will be obtained from external suppliers and the site's finance and procurement records and applied to the resource usage data to provide a cost per study patient. Costs will be measured from the provider perspective and will include the cost of all resources utilized for each study patient, including drugs, laboratory tests, outpatient visits, and fixed costs such as building space, equipment, and management staff. We will estimate the average cost to the provider per patient achieving each primary outcome. The average cost per outcome will then be compared between intervention and standard initiation groups to provide an estimate of the cost-effectiveness of the two

strategies. Costs will be reported as means (standard deviations) and medians (IQRs) in local currencies and dollars.

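### The stated cost methods cannot give a spread for total patient cost (outcome 10), or the cost-effectiveness of one strategy against the other (outcome 11)

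*Protocol*

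**What the plan says.** Protocol section 12b, Secondary outcome 10, sets the first factor: "We will estimate the average cost to patients per clinic visit using questionnaire responses, including transport, substitute labor, and other costs". It then states "This cost will then be multiplied by the average number of clinic visits observed in each study arm", and gives the purpose as "to generate a total average cost to patients of ART initiation under each model (SLATE and standard". It closes with "Costs will be reported as means (standard deviations) and medians (IQRs) in local currencies and dollars". It does not say whether the visit cost is averaged over both arms or within each arm, or which visits are counted.

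The inputs exist for each patient. Section 9d puts the visit-cost questions to every participant, and section 6f places randomization after that questionnaire. Section 9e abstracts dated clinic visits over the whole of follow-up, which is up to 14 months in section 8 and up to 16 months in section 5c.

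Section 12b, Secondary outcome 11, states "At 8 months after study enrollment, all resource usage will be extracted". Unit costs turn this into a cost for each study patient, and then into an average provider cost per patient reaching each primary outcome. Next, "The average cost per outcome will then be compared between intervention and standard initiation groups". The protocol presents this comparison as its estimate of the two strategies' cost-effectiveness. It names no difference in mean cost and no incremental ratio.

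**The concern.** In outcome 10 the method and the promised output do not fit. A product of two averages is a single number per arm, so there is no distribution of total cost to summarise. The product also replaces the mean of individual totals, and the two can differ. Finally, the target is the cost of starting ART, while the visits abstracted run well past that point. If later visits are counted, routine treatment visits enter a figure meant to describe initiation.

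In outcome 11, a programme deciding on adoption needs to know what one more patient started, or started and retained, would cost. A comparison of two average ratios does not answer that. Section 12c sends the results to health departments and donors, who may use them for this decision.

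**Working it through.** The protocol states no cost, visit count or correlation, so there is no figure to reproduce. The costs, coefficients of variation (CVs), correlations and visit counts below are assumed. The rates of 65% and 80% are the planning values in section 11 for patients initiated and retained, and serve only as illustration.

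**Outcome 10: spread.** Arm figure = (average cost per visit) × (average visits). This is one number per arm, so it has no SD, median or IQR. Multiplying each patient's visit cost by the arm's average visits would produce a spread, but it would only be the spread of visit cost on a larger scale, with no variation in visits.

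**Outcome 10: mean.** For visit cost C and visit count V with correlation ρ:

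E[CV] = E[C] × E[V] × (1 + ρ × CV_C × CV_V)

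With CV_C = 1.0 and CV_V = 0.5, true mean divided by product is:

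| ρ | True mean / product |
|---|---|
| -0.3 | 1 - 0.15 = 0.85 |
| 0 | 1.00 |
| +0.3 | 1 + 0.15 = 1.15 |

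Over ρ from -0.4 to +0.3 and CV pairs from (0.5, 0.5) to (1.0, 1.0), the ratio runs from 0.60 to 1.30. A negative correlation makes the product too high, and a positive one makes it too low. The ratio between arms is unaffected if ρ and the CVs match in both arms. If one arm has -0.3 and the other +0.3, the arm ratio is off by a factor of 0.85/1.15 = 0.74 or 1.15/0.85 = 1.35.

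**Outcome 10: which visits.** Assume 3 initiation visits under standard care and 1 under SLATE, plus 12 later visits for each retained patient.

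- Standard: 3 + 12 × 0.65 = 10.8
- SLATE: 1 + 12 × 0.80 = 10.6

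If all visits are counted, a threefold difference in initiation visits almost disappears.

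**Outcome 11.** Average cost per success = cost per patient / success proportion. Incremental cost per extra success = (C1 - C0) / (p1 - p0), with p1 - p0 = 0.80 - 0.65 = 0.15.

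| Cost per patient, standard / SLATE | Average per success, standard | Average per success, SLATE | Cost per extra success |
|---|---|---|---|
| 100 / 110 | 100/0.65 = 153.8 | 110/0.80 = 137.5 | 10/0.15 = 66.7 |
| 100 / 130 | 153.8 | 130/0.80 = 162.5 | 30/0.15 = 200 |
| 200 / 250 | 200/0.65 = 308 | 250/0.80 = 313 | 50/0.15 = 333 |

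In the first row SLATE looks cheaper per success although it costs 10 more per patient. The averages tie when SLATE costs 0.80/0.65 = 1.23 times standard care. A tie could be read as no cost difference, although SLATE would then cost 23% more per patient.

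**The case against.** Several points on the other side stand.

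- The product of averages is exact when visit cost and visit count are uncorrelated, and nothing in the protocol suggests a correlation in either direction. Visit cost is asked before randomization, so that input should not differ by arm. A reader might infer that the cost comparisons will be wrong, or that patient cost will be overstated. The documents support neither.
- The sentence on visits names the cost of ART initiation as its target. A reader might infer that the plan counts every visit and so penalises the better-retained arm. The text does not say this; it leaves the visit window open.
- SDs and IQRs can be given for cost per visit. The gap concerns the total, which is the quantity the outcome names.
- Outcome 11 does build a cost per patient and promises SDs and IQRs, so it would be wrong to say that it has no measure of uncertainty. Cost per success is a legitimate description of each arm, and an incremental ratio could be calculated from the same data.
- A reader might infer that eight months of cost will be divided by the 28-day outcome. The protocol gives the time of extraction but no costing window for each outcome, so this is a possibility only.

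A reader might also extend the point to secondary outcome 8, "Average time to ART initiation (days) for each arm", and infer that never-initiators are left out. No section restricts that average to initiators. The analysis section calls the outcome descriptive ("These will be described using frequencies") and is silent on non-initiators, a detail the statistical analysis plan may settle. Non-initiators do count in the intention-to-treat comparisons of initiation by 14 and 28 days. The inference is not supported.

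What the objection does not remove is that outcome 10 states a calculation that cannot deliver a spread for the total, and outcome 11 gives the name cost-effectiveness to a comparison that does not measure it.

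**Conclusion.** The point holds for outcomes 10 and 11. For outcome 10, the mismatch between method and promised output follows from the text alone and needs no assumption. Any bias in the mean is possible but of unknown size and direction, and the arm ratio is safe if the correlation and CVs are alike in both arms. The visits counted need to be tied to the stated target. For outcome 11, the average ratios are valid as description but do not estimate what one strategy adds over the other at what extra cost. That too needs no assumption; only the size of the gap in the examples rests on assumed costs. The consequence is that the economic results can mislead, not that they must. The primary analyses are not affected.

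**What to change.** **Outcome 10.** Multiply each patient's own reported visit cost by that patient's own number of visits, then summarise by arm with mean, SD, median and IQR. Count visits in one window applied alike to both arms, for example from enrollment to initiation, capped at a common horizon that also applies to patients who never initiate.

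**Outcome 11.** Keep average cost per patient achieving each primary outcome, labelled as descriptive. Add the difference in mean cost per randomised patient and the incremental cost per additional patient achieving each primary outcome, with a bootstrap interval. State a costing window that fits each outcome: 28 days for initiation and 8 months for retention.

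**Cost.** A few sentences in section 12b and a little programming. Visit costs, dated visits and a cost per study patient are already planned for each patient, so no new data are needed.

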#### *6e. Questionnaire*

The study assistant will administer a short questionnaire documenting the subject's basic demographic and socioeconomic characteristics, costs incurred per clinic visit, and preferences regarding ART initiation. As the questionnaire elicits only simple responses and will be completed by the study assistant not the subject, we do not intend to translate the questionnaire itself into subjects' first languages. Instead, for subjects who do not speak English, the assistant will ask the questions in one of the commonly-understood languages used by the study population, and then record the answers in English on the questionnaire. The questionnaire is included in the study case report form in the appendix to this protocol.

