### *9d. Case report form*

The case report form will have eight sections. Sections 1, 7, and 8 will be completed for standard group patients. All sections will be completed for intervention group patients.

1. A short, closed-ended questionnaire to be administered by the study assistant after consent. The questionnaire will elicit basic information about:
  - Patient characteristics (age, sex, marital status, household composition, duration living in current location, education)
  - HIV-related information (familiarity with clinic, time of diagnosis, acquaintance with others with HIV or on ART)
  - Activities and employment
  - Costs to patient of making a clinic visit (transport costs, loss of income, etc.)
  - Patient's preferences regarding ART initiation (single visit, multiple visits, intervals between).
2. Symptom report. The symptom report form will record yes/no to the presence of the symptoms listed above and provide a space for the study clinician to describe or comment on symptoms and to state whether the patient is ineligible for immediate ART initiation due to symptoms.
3. Medical history. The medical history form will record answers to the medical history questions and provide a space for the study clinician to describe or comment on these answers and to state whether the patient is ineligible for immediate ART initiation due to medical history.
4. Physical exam. The physical exam form will record findings of the physical exam and provide a space for the study clinician to describe or comment on these findings and to state whether the patient is ineligible for immediate ART initiation due to the outcome of the medical exam.
5. Readiness assessment. The readiness assessment form will record answers to the readiness questions and provide a space for the study clinician to describe or comment on these answers and to state whether the patient is ineligible for immediate ART initiation due to readiness.
6. Blood draw. The blood draw form will confirm that a blood sample was taken and record the identification number or bar code used to identify the sample on the CD4 count laboratory order form.
7. Patient identifiers. The identification form will capture identifying information about the subject, including name, date of birth, clinic ID number, and national identification number. This information will not be entered into the study database but will be used only for matching CRF and medical record data.

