#### *9e. Medical record data*

Once the CRF has been completed, all remaining patient-level data for the study will be collected from routinely maintained medical records. The format of these records will vary by study country and site. Some sites will use electronic medical records, while others will rely on paper-based records and registers or a combination of electronic and paper. We will access all available records for each study

patient, regardless of format or storage location, to try to obtain as complete a study data set as possible. The fields we will aim to capture are listed below.

*To be used to link electronic and paper-based records to study identification number only:*

- Electronic medical record system number
- Clinic file numbers
- National ID number
- Name
- Date of birth
- Sex

*All subjects at clinic visit on date of study enrollment:*

- Date of positive HIV test (if available)
- CD4 count (most recent)
- Date and result of TB symptom screen, if done
- Date, type, and result of TB test(s) (current and previous, if any)
- TB treatment, if offered (date of initiation)
- WHO stage and clinical conditions

*Subjects who are eligible for ART initiation at the study clinic:*

- Reasons for delaying ART initiation, if relevant
- Date ART initiated (first dose of drugs dispensed)
- First-line regimen prescribed

*For all clinic visits for duration of study follow up, from study enrollment to the follow-up endpoints indicated above:*

- Date of visit
- Primary reason for visit (e.g. pre-ART visit, scheduled medical visit, medication pickup, unscheduled medical visit)
- Types of professionals seen (e.g. nurse, doctor, pharmacy assistant, counselor)
- Group and individual sessions attended (e.g. wellness course, adherence education)
- Numbers and types of all lab tests conducted (including CD4 counts, viral loads, CrAg test, blood tests to determine ARV regimen)
- Other procedures (e.g. x-rays) performed
- Medications prescribed and dispensed (ARV and non-ARV, including isoniazid and cotrimoxazole)
- Admissions for inpatient care since previous visit, if recorded
- Details of inpatient care received (facility, number of days, medications, lab tests, etc.) if recorded

*At follow-up endpoints (6 and 12 months after ART initiation or comparable timepoint for those who do not initiate ART):*

- Date and result of most recent viral load test

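### Outcome 10 multiplies two averages, which gives one figure per arm: it cannot supply the promised SDs, medians and IQRs, and it equals mean patient cost only if visit cost and visit count are uncorrelated

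*Protocol*

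**What the plan says.** Protocol section 12b, under secondary outcome 10, sets out the calculation in three steps.

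- The first factor is an average: "We will estimate the average cost to patients per clinic visit using questionnaire responses, including transport, substitute labor, and other costs".
- The second factor is an arm-level average: "This cost will then be multiplied by the average number of clinic visits observed in each study arm", the purpose being "to generate a total average cost to patients of ART initiation under each model (SLATE and standard)".
- The reporting rule follows: "Costs will be reported as means (standard deviations) and medians (IQRs) in local currencies and dollars".

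No total for an individual patient is formed at any step, although both ingredients are recorded for each patient. Section 6e has the study assistant ask every subject, before randomization, about "costs incurred per clinic visit, and preferences regarding ART initiation". Section 9d places this in CRF section 1, which is completed in both arms. Section 9e abstracts visit-level data from the medical records: "For all clinic visits for duration of study follow up, from study enrollment to the follow-up endpoints indicated above". Section 9f links the two sources by study identification number.

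Secondary outcome 11, the provider cost, ends with the same reporting sentence but is built differently. Unit costs are "applied to the resource usage data to provide a cost per study patient".

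**The concern.** There are two separate difficulties.

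The first is a conflict within the outcome 10 paragraph. It prescribes a calculation that returns one number per arm, then promises summaries that need a value for each patient. An analyst following the text cannot produce the SD, median or IQR of the cost of initiation.

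The second concerns the mean. The average of a product is the product of the averages only when the two quantities are uncorrelated. If patients with costlier visits make fewer of them, the product overstates mean patient cost; if they make more, it understates it.

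Section 4b makes the comparison of patient costs with standard care a stated secondary objective. At stake are the accuracy of the mean in each arm and any description of how costs vary between patients. The primary outcomes are not affected.

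**Working it through.** The protocol states no figure for outcome 10, so there is none to reproduce. The check is of the method.

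**Inputs.** From the protocol: the rule (mean cost per visit times the arm's mean number of visits), the promised summaries, and the fact that both quantities are collected per subject. Not in the protocol, and therefore assumed: a coefficient of variation of cost per visit (k_C) of 0.5 to 1.5, a coefficient of variation of number of visits (k_N) of 0.3 to 0.7, and a within-arm correlation (ρ) of -0.3 to +0.3.

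**Step 1: spread.** Let C be a patient's cost per visit and N that patient's number of visits. The rule gives mean(C) × mean(N), one value per arm. A between-patient SD, median or IQR needs a value for each patient, and the rule creates none.

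**Step 2: mean.** The identity is

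E[C·N] = E[C]·E[N] + ρ·SD(C)·SD(N) = E[C]·E[N]·(1 + ρ·k_C·k_N).

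The relative error of the product of means is therefore 1/(1 + ρ·k_C·k_N) - 1.

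| k_C | k_N | ρ | Calculation | Error of the product |
|---|---|---|---|---|
| 1.0 | 0.5 | -0.2 | 1/0.90 - 1 | +11.1% |
| 1.0 | 0.5 | 0 | 1/1 - 1 | 0% |
| 1.0 | 0.5 | +0.2 | 1/1.10 - 1 | -9.1% |
| 0.5 | 0.3 | -0.1 | 1/0.985 - 1 | +1.5% |
| 0.5 | 0.3 | +0.1 | 1/1.015 - 1 | -1.5% |
| 1.5 | 0.7 | -0.3 | 1/0.685 - 1 | +46.0% |
| 1.5 | 0.7 | +0.3 | 1/1.315 - 1 | -24.0% |

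The last two rows are the extremes of the assumed range.

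**Step 3: comparison between arms.** If ρ·k_C·k_N is the same in both arms, the ratio of arm costs is unaffected and the absolute difference is off by the same percentage as each arm. If it differs between arms, the ratio is distorted too. The protocol does not show which case applies.

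**Step 4: would a half-way calculation do?** An analyst might try to obtain a spread by multiplying each patient's own cost by the arm-average number of visits. I compared this with own cost times own visits in simulated data: 400,000 patients, lognormal cost with mean 5 and k_C of 1.0, and visits averaging about 4 with k_N of about 0.5.

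| Correlation | Product of means | Mean of own totals | SD of own totals | SD using arm-average visits | Median (IQR) of own totals |
|---|---|---|---|---|---|
| -0.22 | 20.0 | 17.7 | 17.7 | 20.0 | 12.6 (7.2 to 22.0) |
| 0.00 | 20.0 | 20.0 | 24.5 | 20.1 | 12.6 (6.6 to 24.1) |
| +0.25 | 19.9 | 22.4 | 33.5 | 19.9 | 12.6 (6.1 to 26.0) |

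The half-way version gives an SD of about 20 whatever the correlation, because it removes all variation in visit number. In this example it is wrong even at zero correlation (20.1 against 24.5), where the mean is right.

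**The case against.** The best defence is that the reporting sentence may refer only to cost per visit, which does have a distribution across patients, and that average unit cost times average visits is a recognisable way to cost a delivery model. Because costs are asked before randomization, a common unit cost also isolates the effect of the number of visits. Part of this stands: the wording allows the reading. But section 12a defines outcome 10 as the cost of ART initiation, so the summaries most naturally describe that total. Even on the lenient reading, the outcome itself is left with no description of its spread.

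A reader might infer three stronger things that the documents do not support.

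- *That the comparison is biased in favour of SLATE, and by a different amount in each arm.* Section 3b says that a process needing many visits burdened patients and deterred many from completing it. That concerns the number of visits required. It does not say that, within an arm, patients with costlier visits make fewer, or that such a link is stronger in the standard arm. A negative correlation is plausible but not shown. Even an invented scenario with dropout rising from 10% to 60% with visit cost gives 26.7 against 16.9 by the product and 24.0 against 15.6 by patient-level totals. The relative saving is then 1 - 16.9/26.7 = 37% against 1 - 15.6/24.0 = 35%.
- *That no confidence interval can be obtained.* A product of sample means has a sampling distribution, and resampling patients or the delta method would give an interval for each arm and for the difference. What is lost is the between-patient spread. Nor does the outcome 10 paragraph promise an interval.
- *That patient-level totals settle the matter.* Cost per visit is asked once, so own cost times own visits still assumes that every visit costs the same.

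**Conclusion.** The point holds in a limited form. The conflict between the prescribed calculation and the promised SDs, medians and IQRs depends on no assumed number, only on reading the reporting sentence as covering the outcome that section 12a names. The product also omits the covariance between cost per visit and number of visits, so it is the mean patient cost only when that covariance is zero.

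The size and direction of any bias cannot be determined from the protocol. The 11% and 9% figures rest on assumed coefficients of variation of 1.0 and 0.5 and correlations of -0.2 and +0.2. Across the wider assumed range the error runs from 46% too high to 24% too low, passing through zero. This is a secondary cost outcome and no primary result depends on it. Since the protocol itself fixes the method and the remedy is simple, the text should be changed.

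**What to change.** Replace the multiplication of averages in section 12b, secondary outcome 10, with a patient-level calculation:

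1. For each subject, multiply the subject's own questionnaire cost per visit by the subject's own number of clinic visits from the medical records.
2. Report the mean (SD) and median (IQR) of these totals by arm and country.
3. Report the arm difference in mean cost with a bootstrap 95% interval, resampling subjects.
4. State that cost per visit is measured once, at baseline, and is assumed constant across a subject's visits.

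This aligns outcome 10 with outcome 11, which already forms a cost for each study patient. The cost is a change of wording and a merge of two data sources already linked by study identification number. No new data are collected.
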